## Abstract

**Background:**

Individuals affected by stroke present with changes in cardiovascular and respiratory functions. Cardiorespiratory training (CRT) is one of the classic intervention guidelines for cardiorespiratory fitness. CRT in association with the proprioceptive neuromuscular facilitation (PNF) technique for respiratory muscles could improve the quality of life, cardiorespiratory function and gait parameters of patients after stroke.

**Objective:**

To assess the effects of respiratory and trunk patterns of CRT associated with PNF on the quality of life, gait, oxygen consumption, respiratory muscle strength and thoracic volumes.

**Methods/design:**

A blind, randomized clinical trial with allocation confidentiality will be performed. Forty patients will be randomized into four groups: CRT-lower limb (LL) plus PNF; CRT-LL and respiration; CRT-upper limb (UL) plus PNF; or CRT-UL and respiration. Individuals will be evaluated at three different times (pretreatment, after 20 days of treatment and 1 month after the end of treatment). The treatment protocol consists of respiratory exercises, 30 min of CRT (cycle ergometer) and then repetition of the respiratory exercises, performed three times a week over a period of 20 days. Primary outcome measures are quality of life, gait, balance, peak oxygen uptake and rib cage compartment volumes. As secondary outcomes, respiratory function and maximal inspiratory and expiratory pressures will be measured.

**Discussion:**

The association of PNF with CRT may be a viable and accessible alternative to increase cardiorespiratory function in patients with stroke.

**Trial registration:**

ClinicalTrials.gov, NCT03171012. Registered on 6 June 2017.

## Background

One of the negative outcomes following the occurrence of a stroke is reduced physical activity [1]. This decrease is a consequence of motor and psychological sequelae after the event [2], which influence the return to activities of daily living [3], work activities and quality of life [1].

Functional deficits are manifested by a lack of control involving several body segments such as the trunk and limb musculature which affect the performance in major and minor movements [4]. In addition, balance and walking speed are diminished in comparison to that expected in healthy individuals of the same age and gender [5], which interferes in activity performance and leads to a functional dependence [6, 7].

The impairment in the skeletal system after stroke affects not only the peripheral muscles but can also involve a decrease in respiratory muscle strength [8], chest wall mobility [9] and postural thorax dysfunction [10]. These impairments together could be related to the decrease in aerobic capacity in this population [11]. Thus, interventions for patients with stroke should be addressed to improve exercise tolerance as well to provide a better adequacy of respiratory muscles.

Respiratory and cardiovascular function are also affected after a stroke [12]. Cardiorespiratory activity is poor in patients with stroke, with peak oxygen uptake (VO_2peak_) measures equivalent to 50–60% of healthy population values for the same age and gender [2]. There is also an increase in the energy cost in daily tasks in those people with functional deficits [5], contributing to reduced social participation [13] and poor quality of life [14]. Maximum oxygen uptake values are also lower than those from healthy individuals [15], as well as other ventilatory parameters such as VO_2peak_ and tidal volume [16].

In addition, this population often has other associated comorbidities such as hypertension and diabetes, which may further delay the recovery of these individuals [17]. Thus, intervention strategies are necessary to interrupt this unfavorable cycle of reduced physical activity, functional capacity decline and increased risk of secondary complications [18].

A home/community physiotherapy program of aerobic and respiratory exercises that could provide increments in the time of active exercise in this population [2] might be attractive to the individual and their family since such a program could reduce the time of intensive rehabilitation and the costs, and restore independence, with a consequent improvement in quality of life [19]. Aerobic exercise training is well known as an effective approach to improve aerobic fitness [20]. Exercises on a cycle ergometer performed for both the upper and lower limbs allow the patient to perform an activity load with a focus on the range of motion, coordination, muscle strengthening and increased exercise tolerance [20, 21]. These exercises are also well tolerated in patients with stroke [22].

As an alternative strategy to stimulate active breathing associated with stretching of the antero-posterior, cranio-caudal and latero-lateral diameters of the trunk, respiratory exercises following the principles of proprioceptive neuromuscular facilitation (PNF) have gained more interest for the treatment of patients with stroke [23, 24]. This approach imposes great awareness of the performed movement on the individual, a factor that is usually not present and which could be helpful in the rehabilitation of patients with stroke [25]. The use of PNF has been traditionally for rehabilitation to address motor impairments related to musculoskeletal parameters such as strengthening and/or stretching of paretic limbs and motor control/motor learning [26]. However, the effectiveness of this technique on respiratory parameters is still little known. In a recent study, respiratory pattern exercises of PNF performed in patients with stroke showed a decrease in bioelectrical activity of the accessory respiratory muscle, which could be related to muscle relaxation and reduction of spasticity and which thus could improve respiratory function [24]. Therefore, we hypothesized that the association of aerobic exercises and exercises with a focus on the respiratory musculature may be a therapeutic alternative capable of improving several functional negative outcomes after a stroke.

The objective of this protocol is to assess the effects of PNF respiratory exercises associated with cardiorespiratory training on respiratory and trunk characteristics, specifically on the quality of life, gait parameters, VO_2peak_, respiratory muscle strength, and thoracic chest wall volumes in patients poststroke.

## Methods/design

This is a prospective, randomized controlled trial with concealed allocation and blinded assessments of patients poststroke (with stroke diagnoses for more than 6 months). Residents living in the community will be recruited from waiting lists of the Physiotherapy Department of the clinical school, as well through disclosures using pamphlets and folders distributed in the community and in social networks including the Communication Agency.

This randomized controlled trial was registered at https://clinicaltrials.gov/ct2/show/NCT03171012 and received approval (65,941,317.7.0000.5537) from the Institutional Ethical Review Board, Universidade Federal do Rio Grande do Norte, Brazil. The study commenced in July 2017 and the estimated completion date is December 2020.  All volunteers will be informed about the objectives, methods and the risks and benefits of the study, and only those who agree to participate by signing an Informed Consent form will be included. The participants will be clearly instructed about the right to refuse to participate in the study at any time of data collection. Intervention procedures and assessment methods do not pose greater risks to volunteers, and will be promptly discontinued in the presence of any reported discomfort. The study protocol was written in accordance with the Standard Protocol Items: Recommendations for Interventional Trials (SPIRIT) guidelines (Additional file 1 shows the SPIRIT checklist). 

### Setting

This study will be carried out in a community-based setting in Recife, Brazil.

### Participants

The inclusion criteria are: primary stroke more than 6 months previously resulting in hemiparesis; age between 21 and 65 years; presence of clinical diagnosis of ischemic or hemorrhagic stroke; absence of cognitive impairment or cognitive deficit (assessed by the Mini-Mental State Examination according to the level of education of participants — less than 19 for illiterate individuals and less than 25 for literate individuals) [27]; being able to walk 10 m independently with or without an assistive device; absence of other neurological or orthopedic deficiencies unrelated to stroke; without reports of associated pulmonary pathology; and not being a current or ex-smoker.

### Participant withdrawal

Patients who miss three consecutive sessions or five intercalated sessions without replacement will be excluded from the study. Also, if the participant reports that they no longer wish to continue they may withdraw from the study at any time.

Participants will be made aware that they are not expected to undergo any other type of physiotherapeutic treatment in order to reduce the risk of interference in the proposed intervention. This requirement will not be enforced in the period between the postintervention evaluation and the follow-up evaluation, but will be recorded if it occurs.

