### Randomization procedures

Block randomization was performed through randomization.com, developed by a researcher who is blinded and belongs to the laboratory but who will not participate in other phases of the study. The researcher will place the identification papers of each group in opaque envelopes and seal them, thus maintaining secret allocation. These envelopes will be delivered to the researcher who will perform the interventions only on the first day of therapy.

The participant and the evaluator will be blinded to the type of breathing exercises performed. Furthermore, contact between patients and their interaction and information exchange about respiratory therapy is minimized since they will be attending at scheduled times with intervals between participants. The researcher who will perform the statistical analysis will be blinded to the treatment groups.

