### Intervention and control

Twenty sessions will be performed with breathing exercises (spontaneous breathing or using PNF patterns), followed by aerobic exercises for lower or upper limbs, and ending with repetition of the respiratory exercises.

The session will begin with the breathing patterns, with each pattern/exercise being performed 10 times. The therapist will position the hands to perform the maneuvers (Fig. 1). In the control group, the patients will put their hands in the same locations used by the therapist during the PNF (Fig. 2).

The cycling will be performed for 30 min per session. Cycling training will be performed without load with a minimum start speed of 50 rpm following the recommendation of the American College of Sports Medicine for patients with stroke [28]. Participants will be encouraged to increase the number of revolutions per minute throughout the study. Thus, participants will perform the cycling at 50 rpm at the beginning; however, there will not be a minimum number of revolutions per minute to reach by the end of the treatment. The patients will be instructed to develop and maintain their highest speed during the exercise, but they may pause if they feel fatigued or need to slow down.

To perform cardiorespiratory training, individuals must be able to remain safe and stable during cycling, with the paretic limb positioned and tied to the pedal. The volunteers will be monitored every 5 min during the 30 min of exercise on the cycle ergometer to check blood pressure, peripheral oxygen saturation and heart rate. The participants will also be asked about their perception of respiratory effort and fatigue in the limbs at the beginning and end of the activity using the original [29] and modified Borg Scale, respectively.

Three evaluations will be carried out at different times: pretraining, post-training and at 30-day follow-up.

The volunteer can be allocated to one of the following protocols:

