### Sample size calculation

The sample size was calculated using the G*Power Program (Version 3.1.9.2, University of Kiel, Germany) and the variable VO_2peak_ (in liters per minute) was adopted as the primary outcome measure. According to a previous study involving individuals with poststroke hemiparesis who performed cycling training [48], standard deviations observed in the experimental and control groups were 0.16 and 0.13, respectively. The sample size was calculated from these data to detect a difference in VO_2peak_ between the groups after intervention of 0.24 l/min (α = 5% and power = 80%), using a two-sample *t* test for mean difference. The sample required was eight patients; considering a follow-up loss of 20%, 10 individuals will be allocated into each intervention group: 10 individuals in the experimental lower limb group (cardiorespiratory training of the lower limbs plus PNF), 10 individuals in the control lower limb group (cardiorespiratory training of the lower limbs plus breathing), 10 individuals in the experimental upper limb group (cardiorespiratory training of the upper limbs plus PNF) and 10 individuals in the control upper limb group (cardiorespiratory training of the upper limbs plus breathing).

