### Statistical analyses

A descriptive analysis of the data will be initially performed. Frequency distribution will be obtained for the categorical variables, and central tendency and dispersion measures will be obtained for the numerical variables. The Kolmogorov-Smirnov/Shapiro-Wilk test and the Levene test will be used to evaluate the normality of the variables and the homogeneity of the sample, respectively.

All tests will be applied assuming a 95% confidence level, considering a significant *P* value <0.05. An intention-to-treat analysis will be performed in case of patient withdrawal or interruption of training, using the last observation carried forward. Two-way repeated-measures analysis of variance to determine the interaction intervention by time (pretraining, post-training and 30 days of follow up) for the outcome variables will be conducted for the experimental and control lower limb interventions and the experimental and control upper limb interventions separately. Paired *t* tests will be used to compare clinical outcomes between preintervention and post-training for experimental and control groups. Independent *t* tests will be also used to separately compare upper limb experimental and control groups and lower limb experimental and control groups post-training.

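### Excluding randomised patients for missed sessions, with no stated further assessment, creates avoidable missing data that the intention-to-treat analysis would fill with baseline values

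*Protocol article*

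**What the plan says.** Protocol article, Participant withdrawal: "Patients who miss three consecutive sessions or five intercalated sessions without replacement will be excluded from the study". A separate sentence in that section covers patients who choose to leave, so the missed-session rule applies to people who have not asked to stop.

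Randomization procedures: "These envelopes will be delivered to the researcher who will perform the interventions only on the first day of therapy". Every missed session therefore comes after randomisation.

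Intervention and control: "Three evaluations will be carried out at different times: pretraining, post-training and at 30-day follow-up". No outcome assessment is scheduled during training.

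Statistical analyses: "An intention-to-treat analysis will be performed in case of patient withdrawal or interruption of training, using the last observation carried forward".

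No section says whether a patient excluded for missed sessions is still invited to the post-training and 30-day assessments, or states in terms that such a patient stays in the analysis set.

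**The concern.** Attendance is a post-randomisation event that may depend on the allocated exercises and on how the patient responds to them. A rule that ends a patient's participation on attendance grounds can be read in two ways.

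- **Removal from the analysis.** This conflicts with the intention-to-treat statement.
- **Removal from follow-up only, with the gaps filled by the last observation.** All randomised patients are then analysed, but those excluded during training contribute no outcome of their own. Their last observation is the pretraining one, so each enters the later visits as a patient who did not change.

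On the second reading the protocol itself produces the missing data that the analysis must fill, among people who might willingly have attended. With 10 patients per arm, each one is 10% of the arm. No later analysis plan can recover an assessment that was never made.

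**Working it through.** **Inputs.** From Sample size calculation: a difference "between the groups after intervention of 0.24 l/min"; standard deviations 0.16 and 0.13 l/min; alpha 5%; power 80%; eight per group, raised to 10 for 20% follow-up loss. Sidedness is not stated; two-sided is assumed.

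**The plan's own figure.** Pooled SD = √((0.16² + 0.13²)/2) = 0.146 l/min, so d = 0.24/0.146 = 1.646 (unrounded SD used). The exact two-sample t test needs 7 per group (power 80.7%); 8 per group gives 86.4%. With the larger SD of 0.16 in both groups, 8 per group gives 79.7%. The stated 8 is reproduced within a patient, and 8/0.8 = 10. The sample size is not in dispute.

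**What carrying forward does.** Let g be the mean gain in the control arm, g + δ the gain in the PNF arm, and q_E and q_C the shares excluded during training in the PNF and control arms. Excluded patients are entered with zero change. Assume that they would otherwise have had their arm's average gain. The expected difference is then

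(1 − q_E)(g + δ) − (1 − q_C)g.

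**Equal exclusion, q in both arms.** This reduces to δ(1 − q). Power is for 10 per arm with the SD unchanged:

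| q (assumed) | Difference, l/min | Power |
|---|---|---|
| 0% | 0.240 | 93.6% |
| 10% | 0.24 × 0.9 = 0.216 | 87.9% |
| 20% | 0.24 × 0.8 = 0.192 | 79.5% |
| 30% | 0.24 × 0.7 = 0.168 | 68.4% |

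The allowance from 8 to 10 replaces lost numbers. It does not offset the dilution from patients who are kept in at their baseline value.

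**Unequal exclusion, no true effect (δ = 0).** The expression becomes (q_C − q_E)g. With 30% excluded in one arm and 10% in the other:

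- g = 0.1 l/min (assumed): 0.2 × 0.1 = 0.02 l/min
- g = 0.2 l/min (assumed): 0.2 × 0.2 = 0.04 l/min

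The false difference goes against whichever arm loses more patients. Against the planned 0.24 l/min it is 0.02/0.24 = 8% to 0.04/0.24 = 17%.

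**How strict the rule is.** Intervention and control says "Twenty sessions will be performed with breathing exercises", which puts the two limits at 3/20 = 15% and 5/20 = 25% of sessions. The abstract has treatment "performed three times a week over a period of 20 days", which is 3 × 20/7 ≈ 8.6 sessions and puts them at about 35% and 58%. These passages must be reconciled before the reach of the rule can be judged.

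**The case against.** The strongest reply is that the passages fit together. The missed-session rule stands under a heading about withdrawal, and the analysis section applies intention to treat to withdrawals and interrupted training. A patient removed under the rule is then one whom the analysis retains. This stands. A reader might infer that the protocol flatly contradicts its own intention-to-treat commitment, but the text does not support that: no sentence removes these patients from the analysis set. Nor would the whole analysis rest on imputed values; only the excluded patients' later visits would.

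The lack of further assessment is also an inference. The article is silent on it, and a condensed article may leave the handling of discontinued patients to the full protocol. That is fair. But exclusion from the study, as opposed to from training, is what the article states, and its ordinary meaning includes the visits.

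Three further points limit the size.

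- The 20% is overall follow-up loss, not a rate of exclusion for missed sessions. Only sessions that are not made up count, so the rule may catch few patients.
- Different exclusion by arm is possible, because the therapist applies resistance in the PNF arms and patients place their own hands in the control arms. Nothing in the article shows that it will happen. Cycling time and the number of breathing repetitions are matched, and participants are to be blinded to the type of breathing exercise.
- Equal exclusion pulls the estimate towards no effect. At 20% the power is still close to the 80% target.

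These points lower the weight of the concern; they do not remove it.

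**Conclusion.** The concern holds in a limited form. As written, the protocol removes randomised patients from the study for missed sessions and does not say that they are still assessed. Read with the analysis section, they most likely remain in the analysis with baseline carried to both later visits. The loss is avoidable and, once assessment windows pass, irreversible.

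The illustrated size is modest: 0.24 falls to 0.192 l/min and power from 93.6% to 79.5% at 20% exclusion in both arms; a false difference of 0.02 to 0.04 l/min arises at 30% against 10%. These figures rest on assumed exclusion rates, an assumed common gain, excluded patients otherwise gaining as much as the rest of their arm, an unchanged SD and a two-sided 5% test. Full measurement would not guarantee 93.6% power, since patients who miss sessions may benefit less.

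A reader might also work out a bias for a comparison of adherers only. The plan names no such analysis, so that figure would not describe the stated one.

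This should be fixed, but it does not by itself undermine the trial. The harm from carrying baseline forward should not be counted again if that method is criticised separately.

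**What to change.** Leave the missed-session limit and its consequence for training as they are. Reconcile Participant withdrawal with Statistical analyses by separating the end of training from the end of study participation:

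- Every randomised patient who has not withdrawn consent is invited to the post-training and 30-day assessments on the original timetable.
- Each is analysed in the randomised arm with the observed data; only withdrawal of consent ends data collection.
- Sessions attended are reported by arm.
- Any analysis restricted to adherers is labelled supportive.

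**Cost.** Recruitment is described as ongoing, so this is an amendment to a running trial. It adds a few visits that would otherwise not take place, and some patients will decline them. Patients already excluded may be past their assessment windows; the report must give their number by arm and how they were handled.

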### Randomization procedures

Block randomization was performed through randomization.com, developed by a researcher who is blinded and belongs to the laboratory but who will not participate in other phases of the study. The researcher will place the identification papers of each group in opaque envelopes and seal them, thus maintaining secret allocation. These envelopes will be delivered to the researcher who will perform the interventions only on the first day of therapy.

The participant and the evaluator will be blinded to the type of breathing exercises performed. Furthermore, contact between patients and their interaction and information exchange about respiratory therapy is minimized since they will be attending at scheduled times with intervals between participants. The researcher who will perform the statistical analysis will be blinded to the treatment groups.

